#### **Primary Objectives**

**Aim 1:** to evaluate the feasibility of the FES for MDD

**Hypothesis 1a:** the overall dropout and protocol compliance rates will not differ significantly between participants randomized to FES or sham-FES.

**Hypothesis 1b:** the overall number of adverse events (AEs) and serious adverse events (SAEs) will not differ significantly between participants randomized to FES or sham-FES.

**Hypothesis 1c:** the nature of AEs and SAEs and the patient experience will not have a significant impact on the dropout and protocol compliance rates.

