**Table 1: Study Schedule**

## 6.2. Randomization and Blinding

Participants will be randomized in a 1:1 allocation to receive FES (active pattern) or FES (sham pattern). Block randomization will be computer-generated, and the samples will be stratified for sex, given the potential differences in response and tolerability in these groups. A biostatistician will generate the randomization schedule, to be administered by a research assistant who is not associated with the study and instructed not to divulge group assignments to the participants to allow for concealment.

Participants and most study staff will be blinded. Only the physical therapist will need to monitor the participant. Measures taken to prevent functional unblinding include sensory and non-patterned sham and delivering automated messages to both active and sham groups. We will also evaluate each participant's ability to discriminate what treatment they received after each session to assess blinding effectiveness.

We will randomize subjects to study arms (20 days active or 20 days sham) using a secure online randomization module on REDCap. The block size will be fixed, and study personnel will be blinded to the randomization block size. An independent assistant, external to the study, will manage the randomization of subjects. The subject number and treatment code will be assigned

after the subject details have been obtained. Based on this information, the independent assistant will assign a unique subject number and treatment code, which will dictate the treatment assignment for the subject. The patterns will be pre-programmed into the take-home device by the biomedical team.

An unblinded code sheet that matches these stimulation codes to the treatment arm will be kept by an external coordinator and will not be available to the study coordinator or research assistants. The unblinded code sheet will have the following information:

1. The initial identifier codes for all potential participants
2. Stimulation code: 6-digit numerical code for the stimulation session
3. Condition number: Numerical code for the condition
4. Condition name: Name of the condition

A copy of this code sheet with the condition name removed will be provided to the study coordinator and research assistants. These linked codes ensure that the study coordinator and research assistants are kept blinded to the type of treatment each participant will receive.

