### FES Visits (20 Visits)

The FES study visits will be conducted at home with personalized masks and a programmable stimulator. Participants will be randomized to undergo either 20 days (weekdays) of FES once a day (20 visits) or 20 days of sham FES once a day (20 visits). Participants will be allowed to miss up to 2 treatment visits. Additional visits will be added on to reach the expected number of visits if it is within a reasonable timeframe as determined by the investigator.

The FES treatment sessions will be 60 minutes in duration (15 min for preparations and 45 min for the stimulation), delivered 5 times/week, for a total of 20 FES sessions. Each FES session will take place over a videoconference. The webcam will be used to record facial expressions during the study because the activation of particular muscles may later need to be confirmed and analyzed. The video recordings are mandatory, and participants' smiles will be detectable through the hollowed-out area around the eyes and the mouth, but only to be viewed by the study personnel for quality assurance purposes. Whenever the FES is on, participants will be required to voluntarily produce the Duchenne smile. Automated messages to voluntarily “smile & hold” (over speakers) precisely timed with the FES-related facial stimulations (only during 15 sec ON times) will be delivered.

Each visit (15 min preparations and 45 min stimulation) will consist of the following:

- A review of FES side effects and adverse events will be completed daily before and after stimulation.
- The users only need to place the mask on their faces and follow the instructions they received at the mask delivery Visit.
- 45 min of FES stimulation to target Duchenne muscles.
- Participant tolerance

- Subjects will be queried each day about their experience and how they are doing. If participants or their family members express that the participant is having difficulty, the study staff will work with them to reduce any possible burden.
- A participant “FES Experience” Assessment will be completed with the subject at the end of each week (Visits 5, 10, 15, and 20) via videoconference to monitor the participant burden.
- Psychiatric interview - will be completed with the subject at the end of each intervention week via videoconference appointment during the 20 days (sessions 5, 10, 15, 20).
  - Hamilton Depression Rating Scale 17-Item (HAM-D-17)

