## **8. Outcome Measures**

### **8.1. Primary Outcome Measures**

The primary outcome will be the feasibility, tolerability, and safety outcomes that include the recruitment, dropout, data completion, and protocol compliance rates, as well as the number and nature of AEs and SAEs. Self-report questionnaires will be completed via REDCap.

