### **14. Data Analysis**

#### **14.1. Sample Size Considerations and Study Feasibility**

For this pilot feasibility trial, we aim to recruit 20 participants in total.

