## **14.2. Clinical Outcomes Analysis**

We are primarily interested in precise estimates of tolerability, outcome variability, and preliminary effectiveness of FES compared to sham FES in patients with MDD that will aid in the planning of a larger, sufficiently powered efficacy trial.

Initial analyses will summarize socio-demographic and clinical characteristics by treatment group. Primary analyses will be performed on the modified intention-to-treat (ITT) population, including all randomized participants that received at least one FES treatment. The feasibility outcome defined as overall dropout rates will be summarized using descriptive statistics such as counts and percentages. Feasibility analyses will report feasibility outcomes using descriptive statistics with counts and proportions for categorical data and means and standard deviations or median and interquartile range, as appropriate, for continuous data. The proportion lost to follow-up will be estimated along with a 95% confidence interval. The lower 95% confidence limit should be at least 90% to proceed. The proportion compliant with the protocol, including treatment compliance as well as study completion and complete data on clinical outcomes will be estimated with 95% confidence interval. For validity to be fairly high, the lower 95% confidence limit should be >90%. The blinding index proposed is scaled to an interval of -1 to 1, 1 being a complete lack of blinding, 0 being consistent with perfect blinding and -1 indicating opposite guessing, which may be related to unblinding.

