The preliminary effectiveness analysis will report the between group difference in change from baseline to treatment 20 in the HAM-D-17 and its 95% confidence interval, using analysis of covariance (ANCOVA), with 20 treatment HAM-D-17 as the outcome and baseline HAM-D-17 and stratification variables (sex) as covariates. We will also report estimates for standard deviation of HAM-D-17 score and within-person correlation between baseline and follow-up HAM-D-17 scores. A similar approach will be used for all other continuous variables for secondary outcome measures (e.g., QIDS-SR, GAD-7, etc). Differences between groups in dichotomous outcomes (e.g., response, remission, adverse effects) will be described using an odds ratio and 95% confidence interval. To explore the sustainability of the treatment effect, we aim to also report changes of HAM-D-17 scores during the month after 20 treatments. The success of blinding of patients will be assessed by computation of Bang's blinding index. Sex and gender stratified analysis will be carried out.

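### The primary adverse-event outcome is a number of events, but the only between-arm adverse-event analysis in section 14.2 is a yes/no odds ratio

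*Protocol*

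**What the plan says.** Section 4, Hypothesis 1b, listed under the primary objectives, states that "the overall number of adverse events (AEs) and serious adverse events (SAEs) will not differ significantly between participants randomized to FES or sham-FES". Section 8.1 completes the list of primary outcomes with "as well as the number and nature of AEs and SAEs"; the Trial Summary and the opening paragraph of section 4 do the same.

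Section 14.2 has two sentences that could bear on this outcome:

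- A general descriptive one: "Feasibility analyses will report feasibility outcomes using descriptive statistics with counts and proportions for categorical data", with means and standard deviations or medians and interquartile ranges for continuous data. It does not name adverse events and gives no contrast between arms.
- A between-arm one: "Differences between groups in dichotomous outcomes (e.g., response, remission, adverse effects) will be described using an odds ratio and 95% confidence interval".

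AEs are collected intensively. In section 6.3, "A review of FES side effects and adverse events will be completed daily before and after stimulation", over 20 sessions. Section 11.1.1 adds daily open-ended questioning and a questionnaire after every session, and records all AEs whatever their attribution.

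**The concern.** The number of events a participant has and whether the participant has any event are different endpoints. Two participants, one with a single episode of redness and one with fifteen, are the same data point in a yes/no table. Hypothesis 1b asks about the first endpoint; 14.2 compares arms on the second. A SAP faithful to 14.2 would leave a primary hypothesis without an estimate.

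The loss matters here because there are many opportunities per person (20 sessions, each with a review) and few persons (about 10 per arm). The sham arm also receives perceptible current through the same setup (section 7.2), so electrode-site reactions are plausible in both arms. Section 14.2 gives precise estimates of tolerability as an aim of the trial, and the count is where most of that information lies.

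**Working it through.** **1. No figure to reproduce.** Section 14.1 says only that "we aim to recruit 20 participants in total". It gives no AE rate, significance level or power. The mismatch in endpoint type is read directly from the text and needs no arithmetic. The calculation below only asks how much the mismatch could cost.

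**2. Inputs.** From the protocol: 20 participants, 1:1 allocation (section 6.2), so n = 10 per arm; 20 sessions. Assumed: per-session AE probability p in each arm, with a threefold active:sham ratio; two-sided 5% level; everyone attends all 20 sessions.

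**3. What the protocol says about p.** It gives no number and points both ways. Section 3 calls redness and soreness common mild events and says that redness or irritation was commonly reported in the open-label MDD pilot. Section 9.2 says that the initial studies, including that pilot, saw no AEs, and that AEs with FES are rare and mild. A wide range of p is therefore shown.

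**4. Formulas.**

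- Any AE, sessions independent: P = 1 − (1 − p)^20.
- Any AE, clustered within person (beta-binomial, concentration k = 5, within-person correlation 1/(1 + 5) ≈ 0.17): P = 1 − ∏ [(1 − p)k + j]/(k + j), for j = 0 to 19.
- Empty cell in the 2×2 table, with A and S the any-AE probabilities for active and sham: 1 − (1 − A^10 − (1 − A)^10)(1 − S^10 − (1 − S)^10).
- Chance of detection: Fisher's exact test on any AE, against a rank test on per-participant counts (simulated).

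Section 14.2 plans estimates, not tests. The detection figures serve only as a yardstick for information retained.

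**5. Worked case, 30% v 10% per session.** Independent: A = 1 − 0.7^20 = 99.9%, S = 1 − 0.9^20 = 87.8%. Clustered: A = 93.8%, S = 58.1%. Empty cell, clustered: 0.938^10 ≈ 0.53 and 0.581^10 ≈ 0.004, giving about 0.53; independent, 0.99.

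**6. Results.**

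| Active v sham, per session | Any AE, clustered | Empty cell: independent / clustered | Detection, clustered: any AE v counts |
|---|---|---|---|
| 30% v 10% | 94% v 58% | 0.99 / 0.53 | 24% v 70% |
| 15% v 5% | 73% v 35% | 0.68 / 0.06 | 22% v 43% |
| 6% v 2% | 40% v 16% | 0.05 / 0.19 | 9% v 21% |
| 1.5% v 0.5% | 12% v 4% | 0.40 / 0.75 | neither informative |

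With independent sessions the detection figures for any AE v counts are 0.4% v 99.9%, 19% v 89%, 21% v 47% and 3.5% v 10%.

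**7. Reading.** Counts keep roughly two to three times the chance of detection in the first three clustered rows. Under the clustered model, empty cells that leave the crude odds ratio inestimable are frequent only at the highest rates, where almost everyone on active has an AE, and at very low rates, where almost no one does.

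**The case against.** **Counts are already covered.** AE numbers sit among the feasibility, tolerability and safety outcomes, and 14.2 promises descriptive statistics for feasibility outcomes. AE counts by arm could well be reported under that sentence. This stands in part: the sentence allows a description, but it does not name AEs or provide a between-arm estimate, and Hypothesis 1b is a between-arm statement.

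**The list is only illustrative, or means each AE type separately.** Possible, but the outcome is still yes/no for each type, not a number.

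**A count model belongs in the SAP.** Usually it would. Here the protocol itself names a method for adverse effects, and that method does not fit its own primary outcome.

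**A stronger reading: the yes/no comparison saturates, so the odds ratio sits near 1 and hides a large difference.** A reader might infer this from 20 sessions and common mild reactions. The documents do not support it. Saturation needs a high per-session rate, about 10% or more in sham, and little clustering; the protocol gives no rate, and section 9.2 points to low ones. At 6% v 2% with independent sessions, any AE is 71% v 33% and the odds ratio about 4.9, with no saturation. Even at 30% v 10% the true any-AE odds ratio is about 11 (clustered) to 173 (independent), further from 1 than the rate ratio of 3. The difficulty at 10 per arm is imprecision or non-estimability.

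**Double counting is already handled.** Section 11.2.2 merges several symptoms of one diagnosis and follows each AE to resolution. That helps, but it gives no rule for one event seen at consecutive reviews, and section 3 says redness can last up to 24 hours.

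**Conclusion.** The mismatch is certain on the text: the primary outcome and Hypothesis 1b concern a number of events, while the only between-arm AE analysis is dichotomous and cannot estimate a difference in number.

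Its cost is conditional. With 10 per arm, a threefold ratio and clustering at concentration 5, the chance of detection falls from about 70% to 24%, 43% to 22%, or 21% to 9% as the assumed rates fall from 30% v 10% to 6% v 2%. At 1.5% v 0.5% neither form is useful. The rates, the ratio and the degree of clustering are all assumptions. The documents do not show that nearly every participant will have an AE or that the planned odds ratio would mask a difference. The correction is worth making because it concerns a primary safety outcome and does not depend on which rate proves true.

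**What to change.** In section 14.2, add as the analysis for Hypothesis 1b:

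- The number of distinct AE episodes per participant divided by sessions attended, by arm, with a rate ratio (or mean difference) and 95% confidence interval from a small-sample method such as a permutation interval. Dividing by sessions attended matters because participants who withdraw early have fewer. The modified ITT population requires at least one treatment, so the denominator is never zero.
- An episode rule: an event continuing across consecutive reviews counts once.
- The counting window. AEs are also collected at Visits 21 to 24, when no sessions are given, so a per-session rate should use events starting in the treatment period, with later ones listed separately.

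Keep the participants with any AE, by severity and relatedness, as a complementary summary; the odds ratio need not be deleted. Reconcile the statements on expected AE frequency in sections 3 and 9.2.

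Cost: a few sentences in 14.2, an episode rule on the AE log and a little more analysis work. No additional data or participants are needed.

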## **15. Publication Policy and Dissemination**

### **15.1. Clinical Trial Registration**

This trial will be registered at [www.clinicaltrials.gov](http://www.clinicaltrials.gov) in accordance with the policy from the International Committee of Medical Journal Editors.

### **15.2. Declaration of Interests**

The Principal Investigators of this trial have no financial or competing interests to declare.

[name] is involved with MyndTec Inc. ([www.myndtec.com](http://www.myndtec.com)) as a shareholder and a director of the company. As a director [name] receives financial compensation for his time on the activity. MyndTec is presently manufacturing the product MyndMove. This is a Functional Electrical Stimulation device for restoring upper limb function in people with upper limb paralysis. Functional electrical stimulation is what we are doing in this study.

[name] has a patent approved February 16, 2016, with [name] and [name] “Functional electrical stimulation method, use and apparatus for mood alteration”. The applicant is the University Health Network. Mood alteration is what we are doing in this study.

[name] is consulting for a company Fourier Intelligence which is designing rehabilitation robotics technologies and receives financial compensation for this activity.

### **15.3. Dissemination Policy**

The results of this trial will be presented at scientific conferences and published, using the CONSORT guidelines, in peer-reviewed scientific journals.

### **15.4. Authorship**

To be eligible for authorship on any resultant publications, all potential contributors must fulfill all criteria as set forth by the International Committee of Medical Journal Editors.

